### Data collection

Most variables will be collected as part of standard of care and are routinely recorded in electronic patients records. The intra-abdominal pressure will be measured by the ward nurse and recorded in the PDMS system and on case record forms (CRF). This CRF contains no patient identifiers. Urine and serum samples will be collected, processed and frozen at −80°C by the researchers or a research nurse. I-FABP and Claudin-3 levels will be measured by the researcher ([name]) and results will be recorded in the CRF. CRFs are stored and secured at the hospital where the patient is included.

### Data management

Research data will be stored in a database (SPSS), and will be handled confidentially and anonymously. Research data that can be traced to individual patients can only be viewed by authorized personnel. These persons are the members of the research team, members of the health care inspection, and members of the Medical Ethics Committee Erasmus MC. The handling of personal data will be in compliance with the Dutch Data Protection Act and the privacy regulation of the Erasmus MC.

Research data will be stored under a code number. Only the code number will be used for study documentation, progress reports and publications. The principal investigator and research assistant are the only persons with the information linking individual persons to study code numbers. Patient data and materials will be stored for a maximum of 15 years after the end of the study. Patients need to consent with this, and if not, their materials will be disposed of upon termination of the study.

### Statistical analysis

Data will be analyzed at the end of the study using the Statistical Package for the Social Sciences (SPSS) version 21 or higher (SPSS, Chicago, Ill., USA) and will be reported following the STrengthening the Reporting of OBservational studies in Epidemiology (STROBE) guidelines. No interim analysis will be done. Normality of continuous data will be assessed by the Shapiro Wilk tests and by inspecting the frequency distributions (histograms). Homogeneity of variances will be tested using the Levene’s test.

Descriptive analysis will be performed in order to report baseline characteristics (intrinsic variables and disease-related variables) and outcome measures of the entire cohort as well as for the group of patients that develop IAH (IAH group; IAP of 12 mmHg or higher on two separate recordings) versus those that do not (control group). For continuous data mean and SD (parametric data) or medians and percentiles (non-parametric data) will be calculated and reported. For categorical data, numbers and frequencies will be calculated and reported for the entire cohort and for the IAH and the control group separately.

Univariate analysis will be performed in order to test the difference in the primary and secondary outcome measures between the IAH group and the control group. Continuous data such as the I-FABP level (primary outcome) of the Claudin-3 level (secondary outcome) will be tested using a Student’s *T*-test (parametric data) or a Mann Whitney *U*-test (non-parametric data). Chi-squared analysis will be used for statistical testing of categorical data such as the number of secondary interventions. A p-value <0.05 will be taken as threshold of statistical significance. Depending upon the number of patients within the cohort of the study that develop ACS and the mortality rate, similar tests will be used to compare data for those who developed ACS (or those who died) versus those who did not. The patient cohort to be included will be heterogeneous by nature, as IAH and ACS risk factors will differ between patients. If it is possible to identify subgroups of patients (*e.g.*, liver transplant patients) subgroup analyses may be performed. P-values <0.05 will be taken as threshold of statistical significance.

The prognostic role of the I-FABP and Claudin-3 on development of IAH, ACS, (increasing) organ dysfunction (based upon SOFA increase) or mortality will be assessed. This analysis will be performed with Stata software, version 10.0 or higher (StatCorp LP, College Station, TX, USA), using the generalized linear latent and mixed model (GLLAMM) framework. Herein, the binary outcome IAH (or new organ dysfuncion or ACS or mortality) will be used as dependent variable, and the level of I-FABP or Claudin-3 will be included in the model as time-dependent variable. Patient ID will be included as clustering variable as up to 13 measurements per patient will be available. Additional covariates such as age, gender, number of IAH risk factors, and BM will be entered into the model in order to evaluate their effect on the relation between biomarker level and outcome. Random intercept and slope will be considered. Results will be expressed as Odds Ratios with their corresponding 95% confidence interval and p-values.

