### Treatment

Patients with increased pressure determined by the intra-bladder pressure measurements will be treated in compliance with the algorithms for patient management as developed by the WSACS (www.wsacs.org/algorithms.php) [3]. The IAH Assessment Algorithm describes all risk factors that every patient should be screened for upon intensive care unit admission and upon clinical deterioration leading to new organ dysfunction. The intra-bladder pressure will be measured in patients with two or more risk factors for IAH or ACS or in patients who have undergone a liver transplantation. Patients who do not have two or more risk factors at baseline but develop new risk factors during their ICU admission will be followed from that moment onwards. The reason for this is that the occurrence of IAH during intensive care stay is known to be an independent predictor for mortality, whereas presence of IAH at intensive care admission is not [23]. Patients should be enrolled as soon as possible, but at least within 48 hours after meeting the eligibility criteria. The IAH/ACS Management Algorithm provides a decision tree for the follow-up of patients related to the IAP level. The IAH/ACS Medical Management Algorithm provides a stepwise approach of actions to be taken for achieving IAP pressure relief. In short, ICU management will be provided by the attending physicians and may consist of, among others, balanced intravenous fluid administration, correction of hypovolemia, electrolyte disturbances and/or anemia and analgesics.

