### Sample size calculation

In order to reliably calculate correlation coefficients for the association between IAP, I-FABP and Claudin-3 levels, at least 75 patients with IAH are needed. Malbrain *et al.* showed in a multicenter study that in a general ICU population, the prevalence of IAH (*i.e.*, IAP > 12 mmHg) and ACS (*i.e.*, IAP > 20 mmHg with concomitant new organ dysfunction) was 32%, and 4%, respectively [23]. Since we will only follow-up on patients with a minimum of two IAH/ACS risk factors, the percentage of enrolled patients that will develop IAH or ACS will be higher, and is likely to exceed 40% (unpublished data). Therefore, enrolling a total population of 200 patients will be sufficient to ascertain availability of 80 patients with IAH.

This will also be sufficient to compare I-FABP levels in patients with physiologic IAP levels with patients that developed IAH with adequate statistical power. Based upon data provided by Kanda *et al*. we expect that mean I-FABP levels will be 20.0 ± 10.0 ng/mL (range 0–100 ng/mL) in patients without IAH [32]. In patients with IAH, the I-FABP levels will be higher (≥20 ng/mL). An overall population of 200 patients (consisting of 120 controls and 80 patients with IAH) will be sufficient to detect a 0.5 SD increase to 30.0 ± 12.5 ng/mL in I-FABP level in patients with IAH (two-sided test with an α level of 0.05) with >90% statistical power.

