## Discussion

Every year, approximately 80,000 patients are admitted to an ICU in the Netherlands [34]. Specific groups of patients such as those who underwent major surgery (*e.g.*, vascular or intestinal surgery) or who sustained severe trauma are at risk of developing morbidity and mortality from postoperative or posttraumatic systemic inflammatory response syndrome, sepsis and multiple organ dysfunction. The development of such potentially lethal complications in relatively healthy surgical or trauma patients is poorly understood. Evidence is accumulating that intra-abdominal hypertension plays a central role in the origin of such postoperative and posttraumatic sequelae. An increased intra-abdominal pressure level is currently the best indicator of intra-abdominal complications. However, the IAP level does not always represent the presence or absence of organ dysfunction, substantial intra-abdominal damage may be present already prior to the development of IAH and ACS. There is a distinctive need for a non-invasive early-onset diagnostic test and biomarkers. The main aim of the current study is to test if urinary I-FABP or Claudine-3 levels can be used as diagnostic tool for identifying patients at risk for IAP-related complications. This marker can then be used in order to take the necessary clinical measures (*e.g.*, decompressive laparotomy) before the IAP has reached the level of irreversible damage to vital organs. This may prevent serious morbidity or even death in a large group patients admitted to the ICU.

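### The IAH group mixes hypertension present at enrolment with hypertension that arises later, so neither the two-group test nor the model for IAH onset can by itself show that I-FABP rises first

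*Protocol article*

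**What the plan says.** In the protocol article, Statistical analysis, the cohort is split in two. One part is "the group of patients that develop IAH (IAH group; IAP of 12 mmHg or higher on two separate recordings"). Every other patient is a control. The univariate analysis will then "test the difference in the primary and secondary outcome measures between the IAH group and the control group", by t-test or Mann-Whitney test. The same section adds a mixed model in which IAH, new organ dysfunction, ACS or mortality is the binary outcome and the biomarker is a time-dependent variable, with up to 13 measurements per patient. Its stated purpose includes the prognostic role of the markers for development of IAH.

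The Sample size calculation section starts from a 32% prevalence of IAH in a general ICU population. For the enrolled patients it says that "the percentage of enrolled patients that will develop IAH or ACS will be higher", likely above 40%, which gives 80 of 200.

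Two other sections show that the authors regard timing as important. Treatment says that "occurrence of IAH during intensive care stay is known to be an independent predictor for mortality", and adds that the same does not hold for IAH found on admission to the ICU. The Discussion says that "substantial intra-abdominal damage may be present already prior to the development of IAH and ACS", and calls for an early test.

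**The concern.** The word *develop* suggests onset under observation, but the rule attached to it only counts raised recordings. If many of the IAH group entered with IAH, a significant difference in I-FABP may show only that patients who already have IAH have higher levels. Reported under the present labels, it would read as evidence that the marker identifies patients who are going to develop IAH. An odds ratio from the mixed model with IAH as outcome could be misread in the same way: a concurrent association would appear as prognosis.

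**Working it through.** **1. Who meets the definition.**
- Study population and eligibility criteria: IAH at entry is not an exclusion.
- Study procedures: IAP is measured at baseline and then every six hours to 72 hours. That is 72/6 + 1 = 13 recordings, and T0 is one of them.
- Statistical analysis: two recordings of 12 mmHg or more suffice, with no condition on T0.

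A patient raised at T0 and at 6 hours therefore joins the IAH group. Reading *develop* strictly, as new onset only, does not help: because everyone else is a control, patients with IAH at T0 would then become controls.

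**2. The model for IAH.** The description names the outcome, the time-dependent biomarker, clustering by patient and covariates. It does not restrict the model to patients still free of IAH, and it sets no order in time between biomarker and outcome. Patients with IAH from T0 onward contribute to the odds ratio.

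**3. The plan's own power.** Inputs from Sample size calculation: 0.40 × 200 = 80 with IAH, 120 controls, difference 0.5 SD, two-sided α 0.05. For the two-sample t-test the noncentrality is λ = d / √(1/n₁ + 1/n₂), with n₁ + n₂ − 2 degrees of freedom:

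λ = 0.5 / √(1/120 + 1/80) = 0.5 / 0.1443 = 3.46, 198 degrees of freedom, power 93.2%.

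The stated figure of more than 90% is reproduced, for the pooled group.

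**4. The same test for new-onset IAH only.** The share of the 80 already raised at T0 is not given, so a range is assumed. Controls stay at 120.

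| Assumed share present at T0 | New-onset patients | λ at 0.5 SD | Power |
|---|---|---|---|
| 10% | 72 | 3.35 | 92% |
| 25% | 60 | 3.16 | 88% |
| 50% | 40 | 2.74 | 78% |
| 75% | 20 | 2.07 | 54% |
| 80% | 16 | 1.88 | 46% |

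About 65 new-onset patients are needed for 90% power (normal approximation), so the stated power no longer applies to new onset once more than about 15/80 = 19% of the group had IAH at T0.

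The section also writes the effect as 20.0 ± 10.0 to 30.0 ± 12.5 ng/mL. That is 10/10.0 = 1.0 or 10/12.5 = 0.8 of the stated SDs, not 0.5. With that difference, power = Φ(10 / √(10²/120 + 12.5²/m) − 1.96) for m new-onset patients: 99.6% for m = 40, 92.5% for m = 20 and 87% for m = 16. The loss of power is serious only at 0.5 SD.

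**5. What pooling can hide (assumed values).** Let half of the 80 have IAH at T0 with I-FABP raised by 1.0 SD, and let the new-onset half show no rise. The pooled difference is 0.5 × 1.0 + 0.5 × 0 = 0.5 SD. Power is 93% if the SD stays at 1. Mixing the two halves widens the group SD to √(1 + 0.25) = 1.12, so λ = 0.5 / √(1/120 + 1.25/80) = 3.23 and power is about 90%. The test would usually be significant with no signal in any patient whose IAH began under observation.

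**The case against.** A reader might infer that the study cannot support early detection at all. The documents do not say so. The stated aim is to identify patients at risk for IAP-related complications, and patients with IAH at T0 are informative for that. The Background describes raised IAP combined with a biomarker as the guide to decompression. The mixed models for new organ dysfunction, ACS and mortality are separate analyses and do not depend on this grouping. No passage presents the univariate test as proof of early detection.

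A reader might also take the Treatment section's statement as a contradiction of the grouping. It is not one. It contrasts IAH at ICU admission with IAH during the stay, for mortality, and is given as the reason for following patients who acquire risk factors later. T0 is enrolment, which may fall well into the ICU stay, so IAH at T0 is not the same as IAH at admission. The statement shows that timing of onset matters to the authors; it is not a rule for a split at T0.

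Subtracting 32% from 40% to get 64 patients with IAH at entry and 16 new-onset is tempting too. The first rate is for a general ICU population and the second for patients with at least two risk factors, so the difference estimates nothing. The 16 above is only the low end of an assumed range.

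Finally, baseline IAP and six-hourly samples are collected and subgroup analyses are allowed, so the split could be made later. That is true, but the subgroup sentence is optional and its example is a patient type (liver transplant), not time of onset. The definition and the label as printed remain wrong for onset. The objections limit the reach of the point; they do not remove it.

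**Conclusion.** The point holds for statements about IAH onset, and only for those. As written, the IAH group contains IAH present at T0 and IAH arising later under one label, and the mixed model for IAH shares the gap. Neither analysis alone can show that I-FABP rises before IAH. Conclusions on organ dysfunction, ACS, mortality and IAP-related complications generally are untouched.

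The problem is mainly one of interpretation. The effect on power depends on two things: the share with IAH at T0, which the documents do not give, and which of the two stated effect sizes is meant. At 0.5 SD, power falls from 93% for the pooled group to between 92% and 46% for 72 to 16 new-onset patients. The correction is cheap and should be made before analysis.

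**What to change.** - **Statistical analysis, grouping:** keep the pooled comparison but call the group patients who *have or develop* IAH. Also report two subgroups, each against the controls: IAH present at T0, and IAH first arising after T0.
- **Statistical analysis, mixed model:** for any early-detection or prognostic statement about IAH onset, restrict the IAH model to patients free of IAH at T0 and use biomarker values measured before onset, for example the last sample before the first IAP of 12 mmHg or more. Patients who stay free of IAH contribute their samples from the same schedule. A T0 sample alone is not enough: the Background gives I-FABP a half-life of 11 minutes, and onset may come up to 72 hours later.
- **Sample size calculation:** replace *will develop* by *will have or develop*. State that the power of more than 90% is for the pooled 80 v 120 comparison, and that the number of new-onset patients is not known in advance.

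**Cost:** wording, one further comparison and a restricted model, all from baseline IAP and six-hourly samples already planned. The new-onset estimate will be less precise than the pooled one and should be reported with its confidence interval.

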### Intra-abdominal pressure and intra-abdominal hypertension

Compliance of the abdominal wall together with the abdominal content determines the intra-abdominal pressure (IAP) level. Under physiologic situations, the IAP level is below 12 mmHg. Increased pressure in the abdomen is known as intra-abdominal hypertension (IAH). This is defined as a sustained IAP ≥12 mmHg [3]. IAH results in reduced blood flow to most organs, with consequent dysfunction of the cardiovascular, respiratory, renal, gastrointestinal, and central nervous systems. An IAP >20 mmHg in combination with new organ dysfunction is indicative of an abdominal compartment syndrome (ACS). The ultimate treatment of ACS is a decompressive laparotomy. Risk factors for ACS include leakage of an aneurysm of the abdominal aorta, closing the abdomen under pressure after abdominal surgery, damage control laparotomy, hyperhydration during hypovolemic shock, pancreatitis, and pulmonary contusion. These risk factors may apply to a majority of patients in the ICU. The mortality risk in patients with ACS may be as high as 80% [1].

The current gold standard measurement tool as put forward by the World Society of the Abdominal Compartment Syndrome (WSACS; http://www.wsacs.org/education/algorithms.html) is an intra-bladder pressure measurement. This is a simple, minimally invasive method, and the results are immediately available [3]. From a clinical perspective, however, the IAP level does not always represent the presence of intestinal ischemia and as such is not a perfect indicator for clinical outcome nor surgical therapy. Sensitive biomarkers indicative of early (*i.e.*, reversible) organ dysfunction are therefore needed as additional diagnostic tool. The combination of increased IAP and a biomarker level that represents organ damage would support the need for and timing of decompressive measures to relieve the abdominal pressure.

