### Biomarkers released upon loss of small intestinal integrity

Evidence is accumulating that the intestines play a central role in the origin of postoperative and posttraumatic sequelae [4-6]. Enterocyte damage and tight junction loss can be triggered by IAH, and both result in loss of intestinal integrity. As a consequence, toxins, bacteria, and undigested food particles may pass the enterocyte layer, enter the underlying vasculature, and trigger systemic inflammatory reactions that may progress to multiple organ dysfunction syndrome and even death. Peptides released upon enterocyte damage (*e.g.*, Intestinal Fatty Acid Binding protein; I-FABP) or tight junction loss (*e.g.*, Claudin-3) are potentially ideal biomarkers that will help identify patients with early IAH-induced intestinal damage.

I-FABP is a small (14–15 kDa) protein that is exclusively present in mature enterocytes of the small and large intestine. It is released into the circulation upon enterocyte membrane integrity loss and rapidly excreted into the urine (half-life 11 minutes). Elevated I-FABP levels have been found in plasma, serum, and urine in patients with intestinal ischemia, celiac disease, systemic inflammatory response syndrome and necrotizing enterocolitis [7-15]. I-FABP levels can be measured sensitively in plasma, serum, and urine using an enzyme-linked immunosorbent assay (ELISA) [7,8].

Claudins are small (22 kDa) tight junction proteins [4,16-19]. Especially Claudin-3 is expressed in high quantities solely in the intestine [18]. The amount of Claudin-3 in the intestine decreases after tight junction integrity loss [17]. Breakdown of tight junctions by loss of Claudins (as measured on Western blots in urine) is an early event in intestinal damage, resulting in intestinal barrier loss [20].

The main aim of the current study is to investigate if urinary levels of I-FABP can be used as a diagnostic tool for identifying patients at risk for IAP-related complications. Secondary aims are to determine the same for serum levels of I-FABP and for urinary and serum levels of Claudin-3.

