### Outcome measures

I-FABP levels will serve as primary outcome measure. Urinary and serum concentrations of I-FABP will be analyzed in duplicate using a highly specific, commercially available enzyme-linked immunosorbent assay (ELISA) that selectively detects human I-FABP (HyCult Biotechnology, Uden, The Netherlands). The ELISA will be performed following the supplier’s protocol. I-FABP levels in urine will be adjusted to urinary creatinine levels.

Claudin-3 levels will serve as secondary outcome measure. Urinary levels of Claudin-3 will be analyzed in duplicate either by ELISA (if available at time of analysis) or by Western blotting. Claudin-3 levels in urine will be adjusted to urinary creatinine levels. If analyzed from Western blots, equal amounts of each sample (adjusted to urinary creatinine levels) will be separated by sodium dodecyl sulphate polyacrylamide gel electrophoresis (SDS-PAGE), transferred to a polyvinylidene fluoride (PVDF) membrane and probed using primary antibody to Claudin-3 (Rabbit anti-claudin-3 (34–1700), Zymed Laboratories, San Francisco, CA). After incubation with goat anti rabbit HRP-conjugated secondary antibody (Jackson, West Grove, PA), a signal will be detected by supersignal west pico chemiluminescence substrate (Pierce, Etten-Leur, the Netherlands). Band intensities for each sample will be semi-quantitatively analyzed using Quantity One (Biorad, Hercules, CA). This is a straightforward approach for semi-quantitative assessment of protein levels. Urinary creatinine levels in the collected samples will be determined at the Clinical Chemistry department.

The occurrence of (increasing) organ dysfunction will be based upon the SOFA score.

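### No stated analysis gives I-FABP's accuracy for IAP-related complications or its value added to IAP: the powered comparison uses groups defined by IAP, and the complication models report only odds ratios

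*Protocol article*

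**What the plan says.** All places are in the protocol article.

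- **Aim** (Background, on biomarkers of intestinal integrity): to "investigate if urinary levels of I-FABP can be used as a diagnostic tool for identifying patients at risk for IAP-related complications".
- **Rationale** (Background, on intra-abdominal pressure): "the IAP level does not always represent the presence of intestinal ischemia and as such is not a perfect indicator for clinical outcome", and "The combination of increased IAP and a biomarker level that represents organ damage would support the need for and timing of decompressive measures". The marker is thus meant to be used together with IAP.
- **Primary outcome** (Outcome measures): "I-FABP levels will serve as primary outcome measure".
- **Group comparison** (Statistical analysis): univariate tests, Student's t or Mann-Whitney, to "test the difference in the primary and secondary outcome measures between the IAH group and the control group". The IAH group is defined by IAP of at least 12 mmHg on two recordings. Similar tests for ACS and death are planned if numbers allow.
- **Sizing** (Sample size calculation): 120 controls and 80 patients with IAH, for a difference in I-FABP level between these two groups. At least 75 patients with IAH are also required so that correlations among IAP, I-FABP and Claudin-3 can be estimated.
- **Prognostic models** (Statistical analysis): mixed models with IAH, new organ dysfunction, ACS or mortality as outcome and time-dependent I-FABP or Claudin-3 as predictor. "Additional covariates such as age, gender, number of IAH risk factors, and BM will be entered into the model". Results are odds ratios with 95% confidence intervals and p-values.

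**The concern.** The aim concerns complications, and the rationale says that IAP alone does not identify them well enough. The comparison on which the sample size rests nevertheless takes IAH, a function of IAP, as the condition that separates the groups. A difference in I-FABP between these groups shows that the marker is associated with raised pressure, which is already measured at the bedside. It does not show that I-FABP identifies patients who will develop complications, or that it says more than the pressure does.

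The mixed models come closer, because they have complications as outcomes. But an odds ratio is not a measure of diagnostic accuracy, and without IAP in the model it cannot separate what I-FABP contributes from what IAP already conveys. At stake is the conclusion: a clearly positive result could be read as support for a diagnostic tool whose accuracy and added value were never estimated.

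**Working it through.** **1. The plan's power figure.** Inputs from the Sample size calculation: n = 120 and 80, two-sided α = 0.05, shift 0.5 SD.

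- Standard error in SD units: √(1/120 + 1/80) = 0.1443.
- Power = Φ(0.5/0.1443 − 1.96) = Φ(1.504) = 93.4% (93.2% with the noncentral t). The stated figure of more than 90% is reproduced.
- With the printed values (20.0 ± 10.0 against 30.0 ± 12.5 ng/mL): SE = √(100/120 + 156.25/80) = 1.669, and power = Φ(10/1.669 − 1.96) = Φ(4.03), above 99.9%.

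The printed 10 ng/mL increase is 0.8 to 1.0 SD, depending on the SD used, not 0.5 SD. That is a separate matter, so both readings are carried forward.

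**2. What such a difference means as discrimination.** Assuming normality, AUC = Φ(δ/√(σ₁² + σ₂²)).

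- Printed values: Φ(10/√(100 + 156.25)) = Φ(0.625) = 0.73.
- 0.5 SD shift: Φ(0.5/√2) = Φ(0.354) = 0.64.
- Smallest observed difference reaching p < 0.05: 1.972 × 0.1443 = 0.28 SD, so AUC = Φ(0.28/√2) ≈ 0.58.

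These AUCs are for telling IAH from no IAH. They illustrate only that a significant difference in level can go with modest discrimination.

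**3. Can the comparison succeed if I-FABP adds nothing to IAP?** Illustrative simulation: 1,000 runs per setting, N = 200, normally distributed IAP with the top 40% labelled IAH. I-FABP is correlated with IAP only as far as needed to give the stated group shift, and the complication depends on IAP alone. *Assumed, because the documents give no figure:* odds ratio 2.5 per SD of IAP, and complication rates of 10%, 20% and 30%. Each patient has one measurement, and ordinary logistic regression stands in for the mixed model.

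| Share of runs with p < 0.05 | Shift 0.5 SD | Shift about 0.9 SD |
|---|---|---|
| I-FABP level, IAH vs control | 93–94% | 100% |
| I-FABP alone, predicting complication | 19–33% | 44–76% |
| I-FABP with IAP in the model | about 5% | 6–7% |

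The group comparison is nearly always positive although I-FABP carries nothing beyond IAP. I-FABP alone also often appears to predict the complication. Once IAP is in the model, the rate falls to about the nominal level.

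**4. Planned analyses against the two questions.**

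| Stated analysis | Accuracy for complications? | Added to IAP? |
|---|---|---|
| I-FABP level, IAH vs control | No, the groups are IAP-based | No |
| Correlation with IAP | No | No |
| Level by ACS or death, if numbers allow | No, difference in level only | No |
| Mixed models | No, odds ratios only | No, IAP is not a named covariate |

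**The case against.** The strongest reply is that the plan does address complications. The mixed models take organ dysfunction, ACS and mortality as outcomes, and the protocol never calls the IAH comparison its primary analysis or ranks the models below it. The covariate list is open, so IAP and severity are not excluded, and accuracy measures are the sort of detail that a condensed article may leave to a fuller plan. A Mann-Whitney statistic divided by n₁n₂ is itself an AUC. All of this is fair. It limits the point to what the article states; it does not supply an analysis that answers either question, and it leaves the sized comparison tied to IAP.

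Four stronger readings are tempting and are not supported:

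- *That the study can show only that I-FABP tracks IAP.* This is true of the one group comparison, not of the whole plan.
- *That performance beyond IAP is the stated aim.* It is the rationale; the aim speaks of patients at risk of IAP-related complications.
- *That leaving out severity biases the odds ratios.* The models assess a prognostic role. A crude prognostic odds ratio is valid for its own question; adjustment answers a different one, incremental value.
- *That the planning values imply a large share of missed complications.* Accuracy figures derived from them concern IAH, and any miss rate needs a specificity that the protocol does not set.

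Replacing the IAH comparison as the sized analysis would also be hard to defend. No event rate for organ dysfunction is given, and the only ACS rate, 4% in a general ICU population, would mean about 8 of 200 patients. The rate in this higher-risk cohort is unknown.

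**Conclusion.** The point holds in a limited form and should be corrected. Followed as written, the plan can establish an association between I-FABP and IAH with high power, and odds ratios for complications. No stated analysis estimates I-FABP's accuracy for complications or what it adds to IAP. That the group comparison can succeed without added value follows from how its groups are defined. The simulated frequencies give only an idea of scale and depend on the assumed odds ratio, complication rates and normality. The AUCs of 0.73 and 0.64 also assume normality, which the quoted range of 0–100 ng/mL around a mean of 20 puts in some doubt. The size of the gap for complications themselves cannot be calculated from the document.

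**What to change.** 1. Keep the IAH-versus-control comparison and its sizing, and state that it shows association with IAH only.
2. For new organ dysfunction (SOFA increase), add to the prognostic analysis the AUC with 95% CI of creatinine-adjusted urinary I-FABP. Use samples taken before the SOFA day on which the increase is scored, because SOFA is daily and sampling six-hourly. Fix one value per patient, or allow for repeated samples in the interval. Give sensitivity and specificity at a cut-off stated in advance or corrected for optimism.
3. Compare a model holding concurrent IAP and baseline SOFA or APACHE II with the same model plus I-FABP (likelihood-ratio test and change in AUC).
4. Report ACS descriptively, or model it without IAP as a predictor, because IAP above 20 mmHg is part of its definition.
5. Base the conclusion about a diagnostic tool on items 2 and 3.

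**Cost.** All variables are already collected, so the change is one of analysis and reporting. The added estimates are not powered, the number of events is unknown, and precision must be read from the confidence intervals. The Study procedures section expects over 95% of IAP-related deterioration in the 12–24 hour window, so some events may have few earlier samples, or none; that number should be reported.
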